##### Objective 1.A and Analysis Plan

The primary outcome will be the days to diagnosis of an HDP, where an HDP is defined as gestational hypertension, preeclampsia, or preeclampsia with severe features. The days to diagnosis of an HDP will be calculated from the date of the first prenatal visit to the date of diagnosis (ICD-10-CM), clinical problem list (SNOMED-CT), and Intelligent Medical Objects (diagnosis and problems). A patient will be considered censored if they are never diagnosed with an HDP. A Cox proportional hazards regression will be used to model the effect of using the digital platform plus RBPM (intervention) compared to the digital platform alone (active comparison) on the days to HDP diagnosis. The regression coefficients and respective *p*-values, and the hazard ratios with confidence intervals will be reported. The predicted survival curves for each group will be plotted, along with the median days to diagnosis for each group. 

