## 1. Introduction

Maternal mortality and severe morbidity events are life-altering tragedies that continue to increase in the United States (US). Maternal mortality rates were 32.9 deaths per 100,000 live births in 2021, compared with a rate of 23.8 in 2020 and 20.1 in 2019 [1]. Pregnancy complications remain the leading cause of death for women aged 20–44, yet another indicator of the sweeping impact of maternal mortality in the US [2,3]. These trends are especially concerning given the United States’ standing as a high-income country. Similar-income countries, such as Canada and the United Kingdom, not only have significantly lower maternal mortality rates but have also seen pronounced decreases within the same time frame [4,5]. 

A critical element in discussions on maternal mortality trends is the prevalent intertwining of social injustice. Consistently, Black and African American (AA) women have been disproportionately impacted by maternal mortality. In 2021, the maternal mortality rate for AA women was 69.9 per 100,000 births, three times the rate when compared to white women [1,6]. Black women frequently report feeling disempowered and discriminated against by their providers during their pregnancies and are more likely to lack access to quality, culturally competent obstetrical and gynecological care than their other-race counterparts [7,8,9,10]. With even Black celebrities and elite athletes unable to escape this profound health crisis [11,12], the burden of maternal mortality among Black birthing persons is immense. Co-existing with maternal mortality trends is the devastating prevalence of cardiovascular disease in the AA community, with nearly 60% of Black women aged 20 and over having a cardiovascular diagnosis [13]. Black women have significantly higher odds of entering pregnancy with chronic hypertension when compared to their white counterparts, and a considerable volume of Black maternal deaths are attributable to hypertension [14,15]. In synergy, maternal mortality and cardiovascular disease disparities speak to the overarching issue of structural racism’s embedment in the US healthcare system, which holds a long, dark history of harming racially marginalized persons [16,17]. 

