### 2.5. Sample Size and Recruitment

The sample size was calculated using PROC POWER in SAS for a two-sided Score test in the Cox proportional hazard regression of the time to diagnosis of an HDP in the study group, with a binary variable taking on the values of intervention (digital platform plus RBPM) or active comparison (digital platform). The proportion of total participants in the intervention group was set at 50%. A hazard ratio of 1.4 for the study group was used as the effect size. The overall probability that a participant would be diagnosed with an HPD was set at 15.9% [43]. The total number of subjects needed to achieve a power of 80% with a significance level of 0.05 was determined to be 1745. 

Overall, HDP affects 15.9% of delivery hospitalizations in the US [43], and the prevalence is higher among patients served by the study site. In 24 months, our system provides prenatal care to over 3000 patients. Given this patient volume and prevalence, we considered the estimated sample size feasible with a 60% enrollment rate, which is consistent with the engagement with prior research studies in our setting of similar durations. We anticipate that the required cohort for each research objective will be enrolled within the desired timeline. The total active participant enrollment time for the planned protocol will be a total of 48 months: 24 months for phase 1, and 24 months for phase 2. 

All people presenting at the study site for prenatal care will be invited to participate at their initial prenatal visit by a study research coordinator. Individuals younger than 18 years will be excluded. Over 35% of patients receiving prenatal care at our facility identify as Black, which will allow us to test for the desired sub-group effects related to social identification. Randomization will occur at the time of enrollment, and baseline measures will be completed. Participants will receive USD 25 at the time of enrollment and each time they complete study data collection (enrollment, and then each subsequent trimester and postpartum) in recognition of the additional time required to complete these study materials. Survey data will be compiled using REDcap 14.2.1, a software distributed by Vanderbilt University in Nashville, Tennessee, United States, for non-commercial secure survey data collection, at enrollment and the subsequent timepoints.

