### 2.7. Data Approach

This study will use data both from the digital platform and the health system’s enterprise EHR. To support the cohort definitions for the randomized trial, digital platform users will be identified by a combination of referrals ordered through the Computerized Physician Order Entry (CPOE) system, matching of contributor systems (i.e., patients with RBPM integration), and industry-standard deterministic matching algorithms. Additionally, the team will use the ICD-10-CM (diagnoses), SNOMED-CT (problems), and Intelligent Medical Objects (diagnosis and problems) coding standards to identify the conditions of interest to support both the time to diagnosis outcome measurements. 

Digital platform data will consist of both manual and automatic data feeds, which will be matched using the approach outlined above. These RBPM readings will be aggregated, and user activity analysis will be aggregated and analyzed with temporal analysis using a multi-paradigm programming language. The number of blood pressure readings and user activity will be correlated with the information in the medical record to establish the relationship between engagement and outcomes. 

Many variables will be defined using EHR data recorded during perinatal care, including demographics, EPDS scores, utilization/engagement, and documentation from the delivery event. These heterogenous data elements are stored in the EHR as structured data to facilitate clean data extraction. They include diagnostics (e.g., lab orders), observations (e.g., vital signs), assessments (EPDS), and medical history (prior diagnoses and chronic conditions). 

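### The fixed covariate list for the Objective 1.A Cox model omits chronic hypertension known at entry, a baseline state that changes which primary events are possible and that the EHR already holds

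*Protocol article*

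**What the plan says.** Section 2.5 invites everyone presenting for prenatal care and states one exclusion: "Individuals younger than 18 years will be excluded". Section 2.3 assigns patients 1:1 with a random number generator, mentions no stratification, and specifies intent to treat.

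Under Objective 1.A the event is any of three diagnoses, "where an HDP is defined as gestational hypertension, preeclampsia, or preeclampsia with severe features", and women never so diagnosed are censored. A Cox model compares the arms. Its covariates are listed in section 2.6.1: age, race, ethnicity, insurance type, gestational age at first visit and number of prenatal visits. Chronic hypertension is not among them, and no stratified model is stated.

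The article treats chronic hypertension as a separate condition. Objective 1.B analyses new diagnoses of it before 20 weeks. The baseline information is available: section 2.4 takes maternal comorbidities from the EHR, and section 2.7 lists "medical history (prior diagnoses and chronic conditions" among the structured data. The Introduction states that "Black women have significantly higher odds of entering pregnancy with chronic hypertension when compared to their white counterparts".

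**The concern.** A woman who enters with known chronic hypertension cannot newly develop gestational hypertension in the usual sense of that term. Her route to the primary event is preeclampsia. The Cox model therefore gives one baseline hazard to two groups that differ in their possible events and probably in their risk.

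Two things are at stake. First, leaving a prognostic factor out of a Cox model pulls the estimated hazard ratio towards 1, even when the arms are balanced, and so costs some power. Second, race is a covariate, and the article itself links race to chronic hypertension at entry. Without the second variable, the race coefficient partly carries the first. That matters for reading the model in a trial whose stated purpose is equity.

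**Working it through.** **Inputs from section 2.5.** A "two-sided Score test in the Cox proportional hazard regression", 1:1 allocation, hazard ratio 1.4, overall event probability 15.9%, power 80%, significance level 0.05, N = 1745.

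**Step 1: reproduce the plan's figure (Schoenfeld).**
Events = (1.960 + 0.842)² / (0.25 × (ln 1.4)²) = 277.31.
N = 277.31 / 0.159 = 1744.1, rounded up to 1745. This matches exactly, so the point does not concern the sample size calculation.

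**Step 2: effect of leaving the factor out.** The article gives neither the share of women with chronic hypertension at this site nor their risk, so both are assumptions. Let c be the share and k their hazard relative to other women. Let g = 1 (comparison) or 1.4 (RBPM), with the same arm effect in both groups. On the scale t of the baseline cumulative hazard:

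- survival in arm g: S_g(t) = (1 − c)·exp(−g·t) + c·exp(−g·k·t), with density f_g(t) = −dS_g/dt;
- the end of follow-up is set so that the average risk over the two arms is 0.159;
- the large-sample Cox estimate β without the factor solves ∫[f_1.4·(1 − w) − f_1·w] dt = 0, where w = S_1.4·e^β / (S_1.4·e^β + S_1);
- power = Φ(½·√277.5·β − 1.96), where 277.5 = 1745 × 0.159.

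Each cell gives the estimated hazard ratio and the power:

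| Share c | k = 0.33 | k = 1.5 | k = 3 | k = 5 |
|---|---|---|---|---|
| 2% | 1.400; 80.0% | 1.400; 80.0% | 1.398; 79.6% | 1.393; 78.8% |
| 5% | 1.399; 79.9% | 1.400; 79.9% | 1.395; 79.1% | 1.384; 77.3% |
| 10% | 1.398; 79.7% | 1.399; 79.9% | 1.391; 78.5% | 1.376; 75.7% |
| 15% | 1.397; 79.5% | 1.399; 79.8% | 1.389; 78.1% | 1.372; 74.9% |

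Check of the worst cell: ½ × √277.5 × ln 1.3715 − 1.96 = 0.67, and Φ(0.67) = 0.749.

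**Step 3: with the factor in the model.** The events needed remain 277.3 and N remains 1745, with power 80.0% at a within-stratum hazard ratio of 1.4.

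**Step 4: the alternative of excluding these women.** If q is their risk of the event, 1745 enrolled leave 1745 × (0.159 − c·q) events.
- c = 2%, q = 10%: 274 events, power 79.5%; enrolment needed 277.31 / 0.157, rounded up to 1767.
- c = 15%, q = 40%: 173 events, power 60%; enrolment needed 277.31 / 0.099, rounded up to 2802.

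Section 2.5 implies about 1800 can be enrolled (60% of 3000). Exclusion costs events and may not be feasible, whereas adjustment costs none.

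**The case against.** The strongest reply is that randomisation balances chronic hypertension in expectation, so the arm comparison is not systematically biased. A Cox model never contains every prognostic factor, and a composite endpoint may include components that some participants cannot have. All of that stands, and it limits the point to precision and interpretation.

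A second reply is that covariate choice belongs in the SAP. This does not answer the point: the article prints the covariate list, and the omission is in what it prints. It is fair to add that a fuller protocol might contain further eligibility criteria.

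Four stronger readings are tempting but not supported:

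- *High-risk women would be censored because superimposed preeclampsia is not named.* On its plain words the definition counts preeclampsia without restricting it to women free of chronic hypertension. The code list is a detail for the full plan. No number of lost events can be derived from the article.
- *The affected events are concentrated among Black participants.* The Introduction gives higher odds in general and no figure for this site.
- *These women are monitored differently.* The caption of Figure 2 ties monitoring frequency to diagnosis, but the figure is not shown, so whether chronic hypertension is one of its categories cannot be seen.
- *Power could fall much further.* If RBPM had no effect in these women and they supplied 5%, 10% or 20% of events, the average hazard ratio, about 1.4^(1 − share), would be 1.38, 1.35 or 1.31, with power 76%, 71% or 61%. That is a difference in effect between groups. A stratified model with one common hazard ratio would not recover it, and nothing in the article suggests it.

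**Conclusion.** The point holds as a modest improvement to a list that the article fixes. Women with known chronic hypertension are eligible, their possible events differ, and the model ignores a baseline state that the EHR supplies. Under the assumed ranges the cost is 0 to about 5 percentage points of power and a hazard ratio of 1.37–1.40 in place of 1.40, plus a race coefficient that is harder to read.

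The result rests on three things outside the article's figures: the usual meaning of gestational hypertension, which the article does not define but which fits the 20-week split in Objective 1.B; the assumed shares and hazards; and 1.4 being the effect within each group, where the plan does not say which effect it means. The largest losses need both a high share and a hazard five times that of other women. With a relative hazard up to 3, power stays at 78% or above.

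**What to change.** Add chronic hypertension documented in the EHR before randomisation (yes/no) to the Objective 1.A Cox model, as a stratum or a covariate. Report the arm effect in women without it as a supporting analysis.

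Use only status recorded before randomisation. Section 2.3 expects RBPM to increase diagnoses of previously unrecognised chronic hypertension, so status learned afterwards would itself be affected by treatment.

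As a clarification only, add a clause confirming that preeclampsia superimposed on chronic hypertension counts as preeclampsia for the primary event.

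The cost is a change of wording. The data are already planned for extraction, and Objective 1.B needs known cases identified anyway in order to count new ones. N stays at 1745. The downside is one stratum that may hold few women and few events; if it is very small, a covariate is the simpler choice.

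### Objective 1.A censors women whose pregnancy ends without HDP, so the planned survival curves overstate the share diagnosed, by an amount that depends on the unstated censoring date, and the planned median does not exist

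*Protocol article*

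**What the plan says.** The primary outcome, in Objective 1.A and Analysis Plan (section 2.6.1), covers gestational hypertension, preeclampsia and preeclampsia with severe features. The clock starts at booking: "The days to diagnosis of an HDP will be calculated from the date of the first prenatal visit to the date of diagnosis". The rule for everyone else is one sentence: "A patient will be considered censored if they are never diagnosed with an HDP". A Cox model gives the hazard ratio, and the absolute display is fixed as well: "The predicted survival curves for each group will be plotted, along with the median days to diagnosis for each group".

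No date is given at which a never-diagnosed woman is censored, and neither delivery nor pregnancy loss is named as a competing event. Section 2.4 collects blood pressure values until 8 weeks after birth, but does not call this the censoring date. Section 2.5 sizes the trial on: "The overall probability that a participant would be diagnosed with an HPD was set at 15.9"%, and on: "A hazard ratio of 1.4 for the study group was used as the effect size".

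**The concern.** HDP so defined arises in pregnancy or shortly after it. A birth or loss without HDP, once any postpartum window has closed, is therefore not a gap in observation. It settles that the event will not happen. At the planned 15.9%, this applies to 84.1% of participants, about 1,468 of 1,745.

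A survival curve treats a censored woman as if she would go on to be diagnosed at the rate of those still at risk. Time runs from the first visit, and gestational age at that visit varies enough to be a listed covariate. Women therefore deliver on different study days, and the risk set can thin while diagnoses are still being made. One minus survival is then not the proportion diagnosed. These curves are the plan's only stated absolute display of the primary outcome, and readers will naturally take them as the percentage diagnosed by a given day. The median is a further problem, because far fewer than half the women in either arm are expected to be diagnosed.

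**Working it through.** **1. The plan's own figure.** Inputs from section 2.5: hazard ratio 1.4, 1:1 allocation, two-sided alpha 0.05, power 80%, event probability 0.159.

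Events (Schoenfeld) = (1.960 + 0.842)² / (0.25 × (ln 1.4)²) = 277.3. N = 277.3 / 0.159 = 1744.1, rounded up to 1745. The stated sample size reproduces exactly. It concerns the hazard ratio test, which can be read as cause-specific with these women censored.

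**2. Does a median exist?** Let p0 and p1 be the shares diagnosed in the comparison and RBPM arms. Under proportional hazards, p1 = 1 − (1 − p0)^1.4, and (p0 + p1)/2 = 0.159. The solution is p0 = 0.1347: 0.8653^1.4 = 0.8166, so p1 = 0.1834, and the mean is 0.159. The arms reach about 13.5% and 18.3%. A median needs 50%, which is 50/18.3 = 2.7 times the higher figure.

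**3. Mechanism.** Let r be the share of the N women still at risk and S the Kaplan-Meier survival just before a diagnosis. That diagnosis raises 1 − KM by S/(rN). Without withdrawals it raises the true share diagnosed by 1/N. Its relative weight is therefore S/r. If nobody has yet been censored, r = S and the weight is 1. Once women leave through delivery, r falls below S. In the simulation below with first visit at 10 (SD 3) weeks and hazard shape 6, S is 0.862 at r = 0.50, a weight of 1.7. At r = 0.10, S is 0.734, a weight of 7.3.

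**4. Size.** Simulation of 400,000 women per scenario, with 15.9% diagnosed by design. Assumptions not in the article: delivery at about 39 weeks; HDP onset from 20 weeks with a Weibull-type hazard of shape 3 or 6; three booking patterns; 0% or 20% of diagnoses in the first 2 weeks postpartum. Entries are (1 − KM) / cumulative incidence, by share still at risk, with non-cases censored at delivery:

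| First visit, weeks | Shape | Postpartum diagnoses | 50% | 10% | 5% | 1% |
|---|---|---|---|---|---|---|
| 10 (SD 1.5) | 3 | 0% | 1.10 | 1.32 | 1.39 | 1.55 |
| 10 (SD 1.5) | 6 | 0% | 1.17 | 1.58 | 1.71 | 1.99 |
| 10 (SD 3) | 3 | 0% | 1.13 | 1.45 | 1.54 | 1.64 |
| 10 (SD 3) | 6 | 0% | 1.21 | 1.72 | 1.90 | 2.13 |
| 12 (SD 5) | 3 | 0% | 1.18 | 1.59 | 1.70 | 1.81 |
| 12 (SD 5) | 6 | 0% | 1.25 | 1.87 | 2.03 | 2.27 |
| 10 (SD 1.5) | 6 | 20% | 1.20 | 1.74 | 2.05 | 2.75 |
| 10 (SD 3) | 6 | 20% | 1.23 | 1.87 | 2.09 | 2.67 |
| 12 (SD 5) | 6 | 20% | 1.26 | 1.94 | 2.19 | 2.64 |

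With non-cases censored at 8 weeks postpartum (shape 6), the ratio is 1.00 to 1.11 throughout, because diagnoses are almost over before censoring begins.

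A second simulation (872 women per arm, diagnosis on average 1.5 weeks before delivery, also assumed) agrees in direction. With censoring at delivery, day 210 shows 19.2% against 14.1% (1.36 times) with tight booking, and 22.3% against 14.2% (1.57 times) with 15% booking after 20 weeks. With 8 weeks of postpartum follow-up the curve ends at 18.1% against 15.9% (1.14 times), or 19.1% against 16.1% (1.19 times) with 5% pregnancy loss.

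**5. Can a median appear anyway?** In the 400,000-woman runs, 1 − KM crossed 50% only when postpartum diagnoses counted but non-cases were censored at delivery (days 238 to 246). The true share in those runs was still 15.9%.

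**The case against.** The strongest reply is that the article does not say women are censored at delivery. The only horizon it mentions runs to 8 weeks postpartum, and on that footing the distortion is small. The choice of estimator is also commonly left to an analysis plan, and the primary inference is sound. Most of this stands, and it limits the size. It does not remove the point: the article itself fixes both the censoring rule and the survival display, and its postpartum window is given for blood pressure readings only.

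A reader might infer more than the documents support:

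- That the curves will show two to three times the true share. This arises only with about 5% or fewer still at risk, and values near three need postpartum diagnoses to count while non-cases leave at delivery. One per cent of 1,745 is about 17 women.
- That the curves cannot be squared with the 15.9%. With 8-week follow-up they end between 15.9% and about 19%.
- That the absolute difference between arms is exaggerated. No two-arm comparison was computed, so this is not claimed.
- That the primary test fails. It does not.

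The simulations also used unadjusted Kaplan-Meier curves, whereas the plan has Cox-predicted ones with gestational age at first visit among the covariates. Adjustment might change the size, which was not tested. It would not change what the curve estimates: diagnosis as if pregnancies did not end.

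On the median, section 2.5 says that HDP is more common at this site, without a figure. Nothing in the article suggests that it approaches 50%.

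**Conclusion.** The point holds for the absolute display. As written, Objective 1.A yields curves whose complement overstates the share of women diagnosed.

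- Non-cases censored at delivery: about 1.2 to 1.3 times with half the women at risk (1.1 to 1.2 with the flatter hazard), and 2 times or more only with about 5% or fewer at risk.
- Non-cases followed to 8 weeks postpartum: about 1.0 to 1.2 times.

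These ranges rest on assumed booking, delivery and diagnosis timing and on a censoring date that the article does not state. The median finding needs only the plan's own 15.9% and 1.4 with proportional hazards: at about 13.5% and 18.3% diagnosed, neither arm has a true median, and any value read from the curves would be produced by the censoring. The cause-specific hazard ratio, its test and N = 1745 are unaffected. The change should be made, but it concerns how the result is shown, not whether the trial can answer its question.

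**What to change.** In Objective 1.A:

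- Keep the Cox model and label its estimate a cause-specific hazard ratio.
- Replace the predicted survival curves with Aalen-Johansen cumulative incidence curves by arm. The competing event is the end of the pregnancy episode without HDP: delivery or loss, or 8 weeks postpartum if postpartum HDP counts. State which.
- Reserve censoring for withdrawal and loss to follow-up.
- Drop the median. Report the between-arm difference in cumulative incidence, with a 95% CI, at a day named in advance.

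The cost is a paragraph of text and standard software. Delivery information already comes from the EHR (sections 2.4 and 2.7), but dates of pregnancy loss would have to be extracted with it. The displayed incidence may look lower than on a survival curve.

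### At the planned 15.9% event probability, the promised median days to diagnosis per group is very unlikely to be reached, so the only planned single-number summary in days would be lost

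*Protocol article*

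**What the plan says.** Objective 1.A (section 2.6.1) makes days to HDP diagnosis the primary outcome. The time "will be calculated from the date of the first prenatal visit to the date of diagnosis", and a woman who is never diagnosed is censored. A Cox model compares the arms and reports coefficients, p-values and hazard ratios with confidence intervals. The section then adds: "The predicted survival curves for each group will be plotted, along with the median days to diagnosis for each group".

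Section 2.5 gives the planning figures:

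- Test: a "two-sided Score test in the Cox proportional hazard regression of the time to diagnosis of an HDP".
- Allocation: "The proportion of total participants in the intervention group was set at 50" per cent.
- Effect: "A hazard ratio of 1.4 for the study group was used as the effect size".
- Event rate: 15.9%, taken from a national source for delivery hospitalizations.
- Result: "The total number of subjects needed to achieve a power of 80% with a significance level of 0.05 was determined to be 1745".

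The same section says that "the prevalence is higher among patients served by the study site", without a number. Section 2.4 collects blood pressure values to 8 weeks postpartum. Objective 1.A does not say on what date an undiagnosed woman is censored.

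**The concern.** The median of a time-to-event curve exists only where the estimated survival falls to 0.50. A plan that expects about 84% of participants to be censored cannot rely on that happening. Section 2.3 hypothesizes that remote monitoring will shorten the days to diagnosis, and the median is the only single number in days that the plan promises for the primary outcome. If it comes out as 'not reached' in both arms, the trial will report a hazard ratio and a plot but no numerical estimate of how much earlier, or how much more often, HDP is diagnosed. A median reached in one arm only, or resting on the last few women at risk, would be worse than none, because it would look like a result.

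**Working it through.** **Step 1. Is 15.9% the operative rate?** Inputs from section 2.5: hazard ratio 1.4, 1:1 allocation, two-sided 0.05, 80% power, event probability 0.159.

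Events = (1.960 + 0.842)² / (0.25 × (ln 1.4)²) = 7.849 / (0.25 × 0.1132) = 277.3.

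N = 277.3 / 0.159 = 1744.1, rounded up to 1745. This is the stated figure, so 15.9% drives the design.

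**Step 2. Proportion diagnosed by arm.** Let p be the proportion in the comparison arm. Under proportional hazards with common follow-up, the intervention arm has 1 − (1 − p)^1.4. Solve

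(p + 1 − (1 − p)^1.4) / 2 = 0.159.

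This gives p = 0.1347 (comparison) and 0.1833 (intervention). The curves end near 1 − 0.1347 = 0.865 and 1 − 0.1833 = 0.817.

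**Step 3. Overall rate needed for a median, with common follow-up.**

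- Intervention arm at 50%: comparison arm 1 − 0.5^(1/1.4) = 0.390; overall (0.390 + 0.500)/2 = 44.5%.
- Comparison arm at 50%: intervention arm 1 − 0.5^1.4 = 0.621; overall (0.500 + 0.621)/2 = 56.1%.

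**Step 4. The censoring date.** The crude proportion diagnosed is not the floor of the curve when censoring is staggered. On a scale of days from first visit, women who book late leave the risk set early, so late diagnoses fall in a shrinking risk set and pull the tail down. A Kaplan-Meier simulation (500 trials, 872 women per arm) checked how far.

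The timing inputs are assumptions, because the documents give none:

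- First visit: mean 11 weeks, SD 4.
- Delivery: mean 39 weeks, SD 1.8.
- Diagnosis: on average 2.5 weeks before delivery and never before 20 weeks.
- With postpartum follow-up: one fifth of diagnoses in the first two weeks after delivery.

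Overall rates above 15.9% are also assumed, to span the unstated site prevalence.

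| Overall rate | Diagnosed, comparison / intervention | Runs reaching 50%, follow-up to 8 weeks postpartum | Runs reaching 50%, censoring at delivery | Median number at risk when 50% is reached, delivery censoring |
|---|---|---|---|---|
| 15.9% | 13.5% / 18.3% | 0% / 0% | 8% / 24% | 4 |
| 25% | 21.4% / 28.6% | 0% / 0% | 42% / 95% | 28 |
| 35% | 30.3% / 39.7% | 0% / 0% | 99% / 100% | 94 |
| 45% | 39.5% / 50.5% | 0% / 97% | 100% / 100% | 196.5 |

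At 15.9% the typical final survival estimate was 0.855 and 0.803 with follow-up to 8 weeks postpartum, and 0.684 and 0.576 with censoring at delivery.

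**The case against.** Several points on the other side stand.

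- **The median is not the primary effect measure.** A reader might infer that the primary analysis fails. It does not: the powered and reported effect is the Cox hazard ratio, which needs no median. The median is a descriptive companion to a plot.
- **The curve could reach 50%.** A reader might infer that the median can never be estimated. The document does not establish that. No censoring date is given, the site rate is said to exceed 15.9%, and with censoring at delivery the table shows usable numbers at risk once the overall rate is well above the planning figure.
- **Nothing proposes a biased estimate.** A reader might infer a median among diagnosed women only, which would compare groups selected after randomization. Objective 1.A does not say this; it keeps undiagnosed women in as censored.
- **The curves are themselves on a days axis.** One minus survival can be read off at any time, so the loss is of a stated number and its interval, not of all information in days.
- **The simulation rests on assumed timings**, and it uses Kaplan-Meier where the plan speaks of predicted curves. Its percentages are illustrative. Steps 1 to 3 do not depend on it.

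None of this rescues the median at the rate on which the trial was planned. An article may also leave the censoring date to a fuller document, so its absence is not raised as a fault in itself. It matters here because whether a median exists turns on it.

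**Conclusion.** The point holds in a limited form. At the plan's own event rate, neither arm comes near 50% diagnosed under common follow-up, and any crossing produced by delivery censoring would rest on about four women. Rescue needs a site rate of roughly 2.8 times the planning figure for one arm (44.5/15.9) and 3.5 times for both (56.1/15.9) under common follow-up. With censoring at delivery a smaller rise suffices, but at an assumed 25% the median would often exist in one arm and not the other. The by-arm figures assume proportional hazards at 1.4. The flaw is in the choice of summary; it does not touch the test, the power or N. It is worth correcting because it is cheap and because the stated hypothesis is about days.

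**What to change.** In Objective 1.A, replace the per-group median with an absolute summary by arm that can be estimated on the plan's own scale of days from first prenatal visit. Either or both of these would serve:

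- the cumulative proportion diagnosed at prespecified times, with a 95% confidence interval for the difference between arms;
- the difference in restricted mean HDP-free days to a prespecified horizon.

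If a percentile is preferred, a low one such as the 10th lies below both expected proportions (13.5% and 18.3%). Fixed gestational ages are better avoided as the time points unless the sponsor also means to change the time scale.

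State the date on which undiagnosed women are censored, since each of these summaries depends on it.

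The cost is one or two sentences of wording and minor extra analysis. No new data are needed, and the Cox model, its test and the sample size stay as they are.
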